**Fig. 2 Fig2:**
[figure not shown]
Nutrition therapy assessment schematic representation. Legend: DEXA = Dual-energy X-ray absorptiometry, F = fruit, V = vegetable, Sat fat = saturated fat, EER = estimated energy requirement, HIIT = high intensity interval training, Std = standard drink, BMI = body mass index

**Table 2 Tab2:** Nutrition recommendations

Food/Nutrient	Serving summary	Recommendation
Total Energy Intake	As specified by your Accredited Practising Dietitian, using the Harris-Benedict equation.	Within requirements
Saturated fat	1 serve = 1 tablespoon of butter, 1 sweet biscuit. Excess fat on meat, full-cream dairy, take-away foods, cakes, bakery items, processed meats, vegetable oil.	<10% total energy
Refined Carbohydrates	Serving size = 1 (40g) Donut, 30g potato chips, 12 hot chips, 1 can of soft drink (375ml), ½ small chocolate bar (25g)	Limit consumption
Whole Grains	1 serve = 1 slice of multigrain bread, ½ cup oats,	4-6 serves per day
Fruits and Vegetables	One serving = 1 medium piece (apple, banana, orange, pear), 2 small pieces (e.g. apricot, kiwifruit, plums), ½ cup of tomato, ½ cup or carrot, ½ cup green beans, ½ cup of pumpkin, 100g mixed frozen vegetables	2 fruits and 5 vegetables per day
Fibre	Aim for 30g/day through your grains, vegetables, and fruit intake	30g/day through grains, fruits and vegetable intake
Lentils/Beans	1 cup per day of cooked or canned legumes/beans such as lentil, chick peas or split peas	1 cup per day
Lean Meats	Lean meats 3-4 times per week. Serving size of 65g include beef, lamb, veal, port, and 80g for chicken, turkey, duck, and 2 large eggs	Lean meats 3-4 times per week
Meats with carcinogenic properties	Red charred meat, visible from over cooking or burning the mean. Processed meats (i.e. salami, sausage)	Reduce or eliminate
Oily Fish	100g per serve of fresh salmon, tuna, trout	2-3 times per week
Dairy	1 cup of fresh, reduced fat milk, or soy milk	2-3 serves per day
Nuts and Seeds	30g (handful) of almonds, cashew nuts, walnuts, macadamia nuts, brazil nuts, pumpkin seed, sunflower seeds	30g per day
Alcohol and discretionary foods	1 standard drink of alcohol = 375ml mid strength beer, 1 glass of wine, 30ml spirit. Discretionary foods = biscuits	0-2 standard serves of alcohol, and reduce or eliminate discretionary foods.

Each participant in the intervention group will be provided with a nutrition pamphlet for supportive education during the study to represent standard dietetic practice. The nutrition pamphlet will be provided at the first dietetic consult and is designed to facilitate the dietetic consultation to help maintain a Mediterranean-style diet pattern. The pamphlet consists of background information about nutrition requirements, optimal nutrition during prostate cancer based on current evidence (kilojoule/cal, fatty acids, carbohydrate, meats and protein, fruits and vegetables, cruciferous vegetables, lycopene, soy isoflavones, vitamin C and calcium, alcohol and discretionary foods) and exercise during prostate cancer treatment. The pamphlet further consists of Decision Balance Tools to help change dietary patterns if needed throughout the dietetic consults by identifying possible barriers to adopting the nutrition therapy. These form part of standard dietetics practice involving motivational interviewing.

Baseline body composition scans (DXA) will classify participants as normal, overweight, or obese state I, according to age specific normative Z values for percentage of body mass index and fat mass [79]. The current diet will be quantified into food groups, total energy intake, and saturated fat intake. From this the diet will be classified as ‘generally healthy’, ‘average’ or ‘poor’ compared to the Australian Dietary Guidelines [80] (as seen in Fig. 2: Nutrition therapy schematic representation). To improve adherence, the nutrition therapy will not be prescriptive, and instead utilize individualized food-based goals with the aim to progressively increase the intake of plant-based foods over the duration of the intervention to meet a modified Mediterranean-style diet pattern.

From weeks 12–20 participants will be required to visit The University of Queensland’s School of Human Movement and Nutrition Sciences three times per week to complete high intensity interval training sessions. Prior to exercising, participants’ heart rate and blood pressure will be measured for contraindications to commence exercising as outlined by the American College of Sports Medicine [81]. The high intensity exercise sessions will commence with 10 min of warm up at 50–70% HR_peak_ before completing 4 x 4 min bouts of cycling at 85–95% HR_peak._ Each 4 min interval will be interspersed with a 3 min period of active recovery at 50–70% HR_peak,_ totaling 38 min for the session. The high intensity exercise sessions will be conducted on an air- and magnetically-braked cycle ergometer (Wattbike Ltd., Nottingham, England). Participants will continue to receive the same dietetic intervention outlined above from weeks 12–20.

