Dietary manipulation has been identified to be an important lifestyle factor to alleviate ADT related side effects [32–34]; yet the efficacy of dietary interventions in isolation during treatment or into prostate cancer survivorship are limited for supporting the adverse side effects seen from ADT. Importantly, prostate cancer-specific dietary guidelines provide limited support and guidance for alleviating adverse treatment-related side effects, including CRF [35, 36]. In non-oncological populations, structured individualized nutrition therapy by an Accredited Practising Dietitian is recommended for adults who are overweight, obese, insulin resistant, and have altered lipid and triglyceride metabolism [37–39]; all notable adverse side effects from ADT. Yet the translation of this nutrition therapy in prostate cancer is yet to be elucidated. Recently, a Mediterranean-style diet pattern has been shown to improve metabolic and cardiovascular parameters in men at risk of prostate cancer [40]. Adherence to an anti-inflammatory properties of a Mediterranean diet have shown small reductions in hypertension (reduced systolic blood pressure; SE = – 1.44mm Hg [95% CI, -2.88 – 0.01]; and diastolic blood pressure; SE = -0.70mm Hg [95% CI, -1.34 – 0.07) [41], and risk of type 2 diabetes (RR = 0.93; 95% CI, 0.89 – 0.98) [42]; thus showing plausible metabolic and cardiovascular effects on known ADT related side effects. Yet practical application of the Mediterranean-style diet pattern to men treated with ADT for management of CRF and improving quality of life is yet to be ellucidated.

Literature to date has encompassed general healthy eating guidelines for the management of prostate cancer treated related side effects [19, 20, 31], however general guidelines do not take into account the specific dietary requirements needed to manage the ADT-related side effects. Therefore, the role of specific individualized nutrition therapy tailored to alleviate the side effects of ADT, particularly CRF, and improve quality of life warrants investigation.

This study aims to:Investigate whether 12-weeks of nutrition therapy, compared to 12 weeks of usual care, can improve prostate CRF and quality of life in men treated with ADT.Assess the combined benefits of 20-weeks of nutrition therapy with 8-weeks of high intensity exercise (weeks 12–20), compared to 20 weeks of usual care, on CRF and quality of life in men treated with ADT.

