### Measurements

All measurements for primary and secondary outcomes will take place at baseline, week 8, week 12, and week 20 (see Table 1). A familiarization trial including the functional capacity and peak aerobic power (V̇O_2peak_) tests will take place at least 7 days prior to baseline testing. Participants will be asked to refrain from vigorous exercise, caffeine, alcohol, food and beverages (except for water) for 12 h before all testing sessions.

**Table 1 Tab1:** Data collection schedule

Assessments	Time (weeks)				
	Baseline^a^		Week 8	Week 12	Week 20
Screening					
Participant eligibility	✓	Randomization			
Adult Pre-exercise Screening System	✓				
Medical history form and medications	✓				
Primary outcomes					
Function Assessment of Cancer Therapy-Fatigue	✓	Randomization	✓	✓	✓
European Organization of Research and Treatment of Cancer QLQ-C30*	✓		✓	✓	✓
European Organization of Research and Treatment of Cancer QLQ-PR25^□^	✓		✓	✓	✓
The Medical Outcomes Study 36-Item Short-Form 36	✓		✓	✓	✓
Second Outcomes					
Anthropometric physique traits	✓	Randomization	✓	✓	✓
Body composition^b^	✓		✓	✓	✓
Isometric strength	✓		✓	✓	✓
Chest and leg one repetition maximum test	✓		✓	✓	✓
Sit to stand test	✓		✓	✓	✓
Six-meter walk test	✓		✓	✓	✓
400-meter walk test	✓		✓	✓	✓
Cardiorespiratory fitness^c^	✓		✓	✓	✓
Blood collection	✓		✓	✓	✓
Wollongong Dietary Inventory	✓		✓	✓	✓
24-h diet recall^d^	✓		✓	✓	✓
Depression Anxiety Stress Scale	✓		✓	✓	✓
Insomnia Severity Index	✓		✓	✓	✓
Physical Activity Enjoyment Scale	✓		✓	✓	✓
Godin Leisure-Time Physical Activity Questionnaire	✓		✓	✓	✓
Accelerometer^e,f^	✓		✓	✓	✓

^a^Nutrition and exercise intervention commences Week 0 after randomisation

^b^Dual energy X-ray absorptiometry

^c^V̇O_2peak_ test

^d^Conducted every 2 weeks

^e^Actigraph GT3X+

^f^to be worn for 7 consecutive days

*Cancer quality of life questionnaire for people with cancer

^□^Cancer quality of life questionnaire for people with prostate cancer

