#### Accelerometer

Participants will be asked to maintain their current level of physical activity outside of the testing sessions for the duration of the study. Physical activity will be objectively assessed using the Actigraph GT3X+ accelerometer (Actigraph, Pensacola, Florida), a small, waist-worn, non-invasive device. Few studies have been published on the validity of the GT3X+ version of the Actigraph accelerometer specifically, however previous versions of the Actigraph accelerometer (CSA and GT1M) have demonstrated waist-worn validity in treadmill walking and running compared with indirect calorimetry (*r* = 0.56, *p* < 0.001 and *r* = 0.53, *p* < 0.05, respectively) in adults [70, 71].

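### Exercise information goes to the intervention arm alone at the first dietetic consult, so a week-12 effect may not be attributable to nutrition alone

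*Protocol article*

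**What the plan says.** Under Interventions (Nutrition therapy with high intensity exercise), the protocol article says: "Each participant in the intervention group will be provided with a nutrition pamphlet for supportive education during the study". On timing: "The nutrition pamphlet will be provided at the first dietetic consult". The list of contents is mostly nutritional but ends with "alcohol and discretionary foods) and exercise during prostate cancer treatment". The Usual Care section describes no such material for controls.

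The first aim in the Background is: "Investigate whether 12-weeks of nutrition therapy, compared to 12 weeks of usual care, can improve prostate CRF and quality of life". The word 'alone' appears in two places. In the Background hypotheses it is attached to nutrition for the secondary measures, and in the Discussion it is attached to nutrition for fatigue.

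Three further statements bear on the point:

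- Interventions, on the training sessions: "From weeks 12–20 participants will be required to visit". The Abstract, the second aim and the opening of Methods/design also place exercise in weeks 12–20.
- Other measures, Accelerometer: "Participants will be asked to maintain their current level of physical activity outside of the testing sessions for the duration of the study". This is not limited to one arm.
- Table 1, footnote a: "Nutrition and exercise intervention commences Week 0 after randomisation".

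Table 1 schedules both the accelerometer and the Godin questionnaire at baseline and weeks 8, 12 and 20.

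**The concern.** Up to week 12 the arms are meant to differ in nutrition therapy only. As written they also differ in exercise information. Of all possible co-interventions, exercise is the one the Background ties most firmly to the primary outcome: it treats the fatigue benefit of aerobic and resistance training as settled, and the evidence for diet by itself as limited. If intervention men became more active in weeks 0–12, part of a week-12 gain in fatigue or quality of life could come from that activity and be reported as an effect of diet. The isolated effect of individual nutrition therapy is one of the two novelties that the Discussion claims.

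The text also pulls in two directions. All men are asked to hold their activity constant, yet one arm is handed exercise material at the start. A reader who takes footnote a literally would conclude that there is no nutrition-only phase.

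**Working it through.** **Passages side by side, weeks 0–12**

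| | Intervention | Usual care |
|---|---|---|
| Dietetic consultations | yes | none described |
| Pamphlet with an exercise topic | yes, at the first consult | none described |
| Supervised interval training | no (weeks 12–20) | no |
| Request to keep activity unchanged | yes | yes |
| Activity measured at baseline, weeks 8 and 12 | yes | yes |

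The second row is the problem. The randomised contrast at week 12 is nutrition therapy including this pamphlet against usual care. That matches the wording of Aim 1. It does not strictly match the word 'alone'.

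**The plan's own figure**

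Inputs from Sample Size Calculation: difference 5.2 FACT-F points, SD 8.9, power 0.8, type 1 error 0.05 (taken as two-sided).

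- Normal approximation: n = 2 × (1.960 + 0.842)² × 8.9² / 5.2² ≈ 46 per arm.
- t-test version: 46.96, so 47 per arm, as stated.

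The sample size reproduces and this point does not alter it.

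**Illustration of what a shift would do**

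The document gives no exercise-related shift, so every value of s below is an assumption, and the range includes zero. With 47 evaluable men per arm, the standard error of the difference is 8.9 × √(2/47) = 1.836 points.

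- Column A: suppose the full 5.2-point difference includes s points from activity. Power for the nutrition part is Φ((5.2 − s)/1.836 − 1.96).
- Column B: suppose nutrition has no effect and activity contributes s. The chance of a significant result in favour of the intervention is Φ(s/1.836 − 1.96).

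| Assumed s (points) | A | B |
|---|---|---|
| 0 | 81% | 2.5% |
| 0.5 | 73% | 4.6% |
| 1 | 63% | 7.8% |
| 2 | 41% | 19% |

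The table shows sensitivity only. It does not estimate what the pamphlet does.

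**Footnote a**

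Read literally, it starts exercise at week 0, while four other places put it in weeks 12–20. Read as the name of the arm's whole programme, it says only that the 20-week programme begins after randomisation. The wording allows both readings.

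**The case against.** The strongest reply is that one topic of background information in a nutrition leaflet is not an exercise intervention. No dose, goal, counselling or supervision is described before week 12, and the behaviour-change tools in the pamphlet are directed at diet. The pamphlet itself is not shown, and its exercise section may simply introduce the later training. The Background also reports a trial in which individual nutrition advice plus half an hour of daily brisk walking over 24 weeks produced no significant change in fatigue or quality of life; a leaflet topic is weaker than that. The request to hold activity constant and the measurements at weeks 8 and 12 are safeguards already in the design. The Usual Care section does not say that controls receive no exercise advice elsewhere. The pamphlet is part of nutrition therapy as the protocol defines it, and the Background hypothesis on fatigue and quality of life does not use the word 'alone'.

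All of this stands, and it limits the point. A reader might infer that the week-12 comparison is contaminated, or that a positive result could not be credited to diet at all. The documents support neither: nothing shows that activity rises, and scheduled data can show whether it did. A reader might also take a shift of 1 to 2 points, 19% to 38% of 5.2, as a likely size. No source in the document supports that range, and zero is plausible.

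The reply does not remove the difference between arms in what they are given, the use of 'alone' in the Discussion for fatigue, or the tension with the activity request. These are things the article states, not details it leaves to a fuller document.

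**Conclusion.** The point holds as a risk to attribution. Giving exercise information to one arm before week 12 may confound the reading of the week-12 effect as that of nutrition alone. Its size cannot be derived from the document and may be zero. The conclusion assumes that the exercise section is delivered with the rest of the pamphlet at the first consult, and that usual care does not routinely supply equivalent information; the article does not settle the second.

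Aim 1 remains a valid randomised comparison of the nutrition package with usual care, and the sample size is unaffected. Footnote a is a matter of wording to be reconciled. It is not evidence that training is planned from week 0.

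**What to change.** 1. Reconcile the pamphlet description with the request to keep activity unchanged by issuing the exercise section separately, once week-12 testing is complete. If it stays in the first pamphlet, describe the week-12 effect as that of the nutrition package and drop 'alone' for that contrast.
2. Reconcile Table 1 footnote a with the intervention text on when the exercise component begins.
3. Report the between-arm difference in accelerometer and Godin activity at weeks 8 and 12, with confidence intervals, next to the Aim 1 result. Use it to interpret that result, not as a covariate: activity after randomisation may itself respond to the diet, so adjusting for it would not isolate a diet effect.

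The cost is a pamphlet printed in two parts, one corrected footnote and a small extra analysis. No new data are needed.

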#### Usual Care

Participants randomized to usual care will continue their usual medical care during this period. Participants in the usual care group will be monitored for 20 weeks and perform identical primary and secondary outcome measures at the same time points as outlined above for the intervention group.

### Sample Size Calculation

Sample size calculations were complete using Vanderbilt Power and Sample Size software (Vanderbilt University, TN). Combined diet and exercise interventions with CRF as an outcome are relatively limited. A diet and exercise intervention in men treated with ADT showed prostate cancer-specific CRF (as measured by FACT-F) scores improved by 3.7 – 14.2 (CI, 95%; adjusted mean 8.9 points) in the intervention group compared to the control group [20]. Assuming FACT-F scores for this group were normally distributed with a SD of 8.9, a true difference between the experimental and control arms of 5.2, and a power of 0.8, we would need 47 experimental and control participants to be able to reject the null hypothesis. The type 1 error probability associated with this test of the null hypothesis is 0.05. With an anticipated 20% attrition rate based on previous research from our laboratory, we would need 58 experimental and control group participants to be able to reject the null hypothesis.

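### The SD of 8.9 and the difference of 5.2 behind the sample size appear to be transposed from the cited trial's effect estimate and confidence interval, so the stated 80% power is unsupported

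*Protocol article*

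**What the plan says.** Everything needed is in the Sample Size Calculation section of the protocol article. It describes one earlier diet and exercise trial in men on ADT, whose FACT-F "scores improved by 3.7 – 14.2 (CI, 95%; adjusted mean 8.9 points) in the intervention group compared to the control group". That is a between-group effect of 8.9 points with its 95% confidence interval.

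The next sentence sets the planning inputs, taking FACT-F scores in that group to be "normally distributed with a SD of 8.9, a true difference between the experimental and control arms of 5.2", with power 0.8. On significance, "The type 1 error probability associated with this test of the null hypothesis is 0.05"; sidedness is not stated.

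The result is that "we would need 47 experimental and control participants to be able to reject the null hypothesis". Attrition of 20% raises this to 58 per group, which gives the total of 116 in the Abstract and in Methods/design.

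The section gives no other source for the SD and no reason for choosing 5.2. It ties the SD to the group in the cited trial.

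**The concern.** Both inputs can be read off the cited result, and both have changed role. The number 8.9 is a treatment effect in one sentence and a standard deviation in the next. The number 5.2 is the distance from the estimate to its lower confidence limit, and it reappears as the treatment effect. A confidence limit's distance from the estimate measures the earlier trial's imprecision; it is neither an effect estimate nor a clinically meaningful target.

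The 47, the 58, the 116 and the 80% power all follow from these two numbers. FACT-F is a primary outcome, and this is the only justification given for the size of the trial. If the inputs are transposed, the reader does not know what difference the trial was designed to detect, or with what probability.

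**Working it through.** **Inputs, all from the Sample Size Calculation:** cited difference 8.9, 95% CI 3.7 to 14.2; planning SD 8.9; planning difference 5.2; power 0.80; type 1 error 0.05; 47 per arm; attrition 20%. Allocation is 1:1 (Randomisation section).

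**Step 1: reproduce the plan's figure.** A two-sided two-sample t test with standardised difference 5.2/8.9 = 0.584, alpha 0.05 and power 0.80 needs n = 46.96, so 47 per arm. Power at 47 is 0.800. A one-sided test would need 37 (normal approximation), so the calculation was two-sided. Attrition: 47/0.8 = 58.75, against the stated 58; that is rounding and not part of this point. The stated inputs were used, and the arithmetic on them is sound.

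**Step 2: compare the inputs with the cited result.**
- Planning SD 8.9; cited adjusted mean difference 8.9. Identical.
- Planning difference 5.2; 8.9 − 3.7 = 5.2. Identical to the lower arm of the interval. The upper arm is 14.2 − 8.9 = 5.3 and the symmetric half-width is (14.2 − 3.7)/2 = 5.25, so the interval is symmetric up to rounding.

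**Step 3: what SD the interval does imply.** For a simple two-arm comparison with n per arm, SE = 5.25 / t(0.975, 2n − 2) and SD = SE × √(n/2). The cited trial's size is not in the article, so n is an assumption and a range is shown. Example at n = 25: SE = 5.25/2.011 = 2.61; SD = 2.61 × √12.5 = 9.2.

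**Step 4: power and detectable difference with 47 completers per arm.** Power is from the noncentral t, two-sided 0.05. The difference detectable with 80% power is 0.584 × SD.

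| Assumed n per arm, cited trial | Implied SD | Power for 5.2 | Power for 8.9 | Detectable difference at 80% |
|---|---|---|---|---|
| 15 | 7.0 | 94% | >99% | 4.1 |
| 20 | 8.2 | 86% | >99% | 4.8 |
| 25 | 9.2 | 77% | >99% | 5.4 |
| 30 | 10.2 | 69% | 99% | 5.9 |
| 40 | 11.8 | 56% | 95% | 6.9 |
| 50 | 13.2 | 47% | 90% | 7.7 |

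The implied SD is close to 8.9 when the cited trial had about 23 per arm (8.8 at n = 23). If 8.9 points were the intended target, between 11 and 36 per arm would suffice for 80% power over the same range of SDs.

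**The case against.** The best case for the protocol has four parts.

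- **The transposition is inferred.** The section says only that an SD of 8.9 is assumed, and the cited paper, which is not at hand, may report such an SD. This stands as a limit on wording: the inputs appear to be transposed. But two matches at once, each with the wrong role and in adjacent sentences, are hard to put down to chance. Even if they were chance, the article would still give no support for either input.

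- **The value 8.9 may be about right.** It lies inside the implied range of 7.0 to 13.2, and the resulting powers fall on both sides of 80%. This stands. A reader might infer that the trial is too small, and the document does not show that. Against the one effect estimate it quotes, 8.9 points, 47 per arm is ample at most of the SDs considered and still gives about 90% power at the largest.

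- **A null result would remain readable.** A reader might infer that a null FACT-F result could not be interpreted. That does not follow. Such a result is read from the observed difference and its confidence interval, which use the observed SD. With 47 per arm the 95% half-width is about 0.41 × SD, or 2.9 to 5.4 points over the range above, so an estimate near zero would exclude an effect of 8.9.

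- **The back-calculation is approximate.** The cited interval is for an adjusted difference, so the implied SD need not equal the raw SD, and it is not a strict floor or ceiling. The Statistical Analysis section also lists repeated measures ANOVA, whose power may differ from that of a t test. Both points stand, and they are further reasons to give a range.

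A condensed article may leave the rationale for a target difference to the full protocol, so its absence alone would not be a finding. What is at issue is a conflict in the printed text: the same number appears as an effect and then as an SD, and a confidence-interval distance appears as the effect.

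**Conclusion.** The point holds as a problem with where the inputs come from, not as an arithmetic error. The calculation is correct given its inputs, but those inputs appear to be transposed from the cited result, and nothing in the article supports 8.9 as an SD or 5.2 as a target difference. The stated 80% power is therefore unsupported.

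The direction of any error is unknown. Assuming 15 to 50 per arm in the cited trial and treating its interval as that of a simple two-arm comparison, power for 5.2 points lies anywhere from about 94% to 47%. Power for 8.9 points stays at about 90% or more. Because this is the sole justification of the sample size for a primary outcome, the paragraph should be corrected. The finding does not show that 116 men are too few.

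**What to change.** Rewrite the Sample Size Calculation paragraph:

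1. Take the FACT-F standard deviation from the SDs reported by the cited trial, or derive it from that trial's confidence interval and per-arm size, and show the derivation.
2. Justify the target FACT-F difference separately, for example as a clinically important difference, and not from the width of a confidence interval.
3. State that the test is two-sided, and restate the power, or the detectable difference, for 47 completers per arm over a plausible range of SDs. Over the range used here, the detectable difference at 80% power is about 4.1 to 7.7 points.

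The cost is one paragraph and a recalculation. Recruitment need not change. The downside is that the restated power may be less favourable than 80%.
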